**Apatinib-related proteinuria classification standard (NCI-CTCAE4.0) and recommendations for prevention and treatment**

| Grading | Definition | Prevention and treatment recommendations |
| --- | --- | --- |
| Grade 1 | Urine protein (+)  Or 24-hour urine protein quantification < 1.0g | Continue to take apatinib without dose adjustment;  Pay attention to observation |
| Grade 2 | Urine protein (++)  Or 24-hour urine protein quantification: 1.0-3.4g | a. Continue to take apatinib, generally no dose adjustment required;  b. Drug intervention should be considered;  c. Monitor 24-hour urine routine and 24-hour urine protein quantification |
| Grade 3 | 24-hour urine protein quantification ≥ 3.5g | a. Suspend taking Apatinib;  b. Consult with a specialist in nephrology;  c. Conduct drug intervention;  d. After proteinuria returns to ≤2 grade, the dosage of Apatinib can be reduced;  e. If grade 3 proteinuria still occurs after 2 dose reductions, the Apatinib treatment shall be permanently terminated |

### 3.7.3. Hand-Foot Skin Reaction

**HFSR classification standard (NCI-CTCAE 4.0)**

| Grading | Definition |
| --- | --- |
| Grade 1 | Minor skin changes or dermatitis (local erythema, edema, hyperkeratosis, painless) without affecting daily life |
| Grade 2 | Obvious skin changes (flaking, blisters, bleeding, swelling, hyperkeratosis), pain, affecting daily life and activities |
| Grade 3 | Severe skin changes (flaking, blisters, ulcers, bleeding, edema, hyperkeratosis), obvious pain, with limited personal self-care ability |

Suggestions: Early prevention of HFSR can lower the severity of adverse reactions. Therefore, from the first day of taking Apatinib, do not wait until the HFSR occurs, the following is recommended:

1. Patients are recommended to avoid squeezing their hands and feet, to wear loose and soft shoes, and to avoid stimulation by excessive cold and heat;
2. Patients are recommended to apply urea ointment / moisturizing cream or aloe vera gel to the hands and feet on the first day of taking Apatinib.
3. If HFSR has occurred, skin care shall be strengthened to keep the skin clean to avoid infection. When the skin is not damaged, magnesium sulfate solution (1-3%) or honeysuckle of 50 g may be used to soak hands and feet in water for 10-15 minutes each time, the moisture can be absorbed with a soft towel, then urea ointment can be applied for moisturizing.
4. B vitamins can be taken appropriately. If it is difficult to relieve the pain, Celecoxib can be taken.
5. When intolerable pain occurs, it is recommended to stop taking Apatinib, and wait for 2 to 3 days after stopping the drug, and resume the drug after the pain is relieved.. Recovering medication after stopping will generally reduce the degree of pain.

### 3.7.4. Skin Rash

Skin rash usually appears about 1 week after medication. It is most obvious in the dorsal joints of the limbs, such as the elbow, wrist, knee, and ankle joints. It may manifest as macule, papules, pruritus, desquamation and ulcers, most of which will disappear within 1 to 2 weeks after appearance.

Treatment method: a. External use: Compound Dexamethasone Acetate, Eloson, calamine lotion, mupirocin ointment; b. Oral: anti-allergic drug such as Clarityne

### 3.7.5. Bleeding

Patients using the drug should be closely monitored for coagulation function, and in case of severe abnormal coagulation function (grade 3 to 4), drug suspension is suggested. If massive gastrointestinal bleeding occurs, Apatinib must be discontinued immediately, and bleeding should be treated actively based on conventional clinical practice.

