A multicenter phase II clinical study ^[19]^ found that adding bevacizumab to standard chemo-radiotherapy for locally advanced NPC patients can delay the progression of subclinical NPC, and this regimen did not cause hemorrhage in Grade 3-4 patients. During the follow-up of 2.5 years (median), the two-year PFS rate was 74.7%, the two-year distant metastasis-free survival (DMFS) rate was 90.8%, and the two-year OS was 90.9%. Therefore, bevacizumab demonstrates certain advantages in both PFS and OS. According to a study where the recurrent or metastatic head and neck cancer/NPC patients were treated with sorafenib monotherapy ^[20]^, among 27 cases, there were 1 case of PR and 10 cases of SD, and mOS was 4.2 months. This indicated the limited efficacy of the sorafenib monotherapy and a combination with chemo-radiotherapy might be required. In another study of sorafenib combined with cisplatin and fluorouracil ^[21]^, 54 recurrent or metastatic NPC patients were treated with the combination therapy, mPFS was 7.2 months and mOS was 11.8 months, suggesting that the combination of sorafenib with chemotherapy is a feasible regimen for the treatment of metastatic NPC. A single-arm exploratory study of single-agent sunitinib [22] found that 10 out of 14 patients received imaging assessment at least once and tumor reduction was found in 5 cases, but 2 cases with tumor invasion of the carotid sheath died of hemorrhage during the experiment, and the possible cause might be the rupture of large cervical vessels during tumor regression.

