### 3.4.4. Withdrawal Criteria

In case of any of the following circumstances, the investigator should discontinue the study and ask the subject to withdraw from the study. Before withdrawal, the investigator should complete the latest evaluation of all indicators, and record in detail the reason and date of the subject's withdrawal.

1) The subject voluntarily withdraws the Informed Consent form and ask to withdraw from the study;

2) The subject has disease progression with medical imaging evidence (e.g., CT, MRI examination results), or clinical progress clearly judged by the investigator (need to record the reasons to judge progress in detail);

3) The subject gets pregnant during the study;

4) The subject delays medication for over 4 weeks;

5) The subject is intolerant to drug toxicity;

6) The subject develops unexpected or unacceptable drug-related adverse reactions;

7) The subject is complicated by other diseases, and is not suitable to continue the clinical study at the investigator's judgment;

8) The subject is poorly compliant, and fails to take drugs on time and at the required dose, or fails to follow the procedures of the study;

9) Other circumstances where the investigator believes it is necessary to ask the subject to withdraw from the study.

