## 3.6. Dose Delay and Adjustment

The dose of Apatinib and Capecitabine can be reduced in the study. For Apatinib, the reduction levels are from 500 mg once daily to 500 mg and 250 mg on alternate days, to 250 mg once daily. For capecitabine, 25% and 50% dose reduction will be given. If the subject is still intolerant to the toxicity after the dose is reduced, he/she should be excluded from the study. During the entire study period, the dose is allowed to be reduced at most twice, and shall not be increased.

The drug can only be suspended or its dose can only be reduced when a subject has grade III or worse adverse events or grade II intolerable toxicity assessed by the clinicians. Controllable nausea, vomiting and fever (below 38°C) with a clear cause can be actively handled and treated symptomatically without suspending the drug or reducing its dose. The dose and suspension of the drug should be stated in the final study report.

To ensure the drug intensity to the subjects in the trial, the time of each drug suspension and the cumulative time of suspension during each administration cycle shall not be over 14 days, and the suspension shall not exceed two times during each cycle. If the drug discontinuation time or the number of suspensions exceeds the requirement, the subject will withdraw from the study, but his/her tumor shall still be evaluated following the study procedure.

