**Grading criteria and prevention and treatment recommendations for hypertension (NCI-CTCAE 4.0)**

| Grading | Definition | Prevention and treatment recommendations |
| --- | --- | --- |
| Grade 1 | Systolic pressure of 120 to 139 mmHg  Or diastolic pressure of 80 to 89 mmHg | Closely monitor the blood pressure; limit salt intake, and quit smoking and alcohol;  Continue to use Apatinib without dose adjustment |
| Grade 2 | Systolic pressure of 140 to 159 mmHg  Or diastolic pressure of 90 to 99 mmHg | Closely monitor the blood pressure; continue to use Apatinib without dose adjustment in normal cases; Should take anti-hypertension drugs and should not discontinue anti-hypertension drugs at will |
| Grade 3 | Systolic pressure ≥ 160 mmHg Or diastolic pressure ≥ 100 mmHg | Suspend Apatinib; Single-agent poorly controlled hypertension, combined medication should be considered;; consult and receive treatment from cardiovascular specialists; closely monitor the blood pressure; reduce the dose of Apatinib and continue to use it if the blood pressure is well controlled |
| Grade 4 | Life-threatening (malignant hypertension or persistent nerve injury, hypertensive crises) | Discontinue Apatinib immediately and permanently; consult cardiovascular specialists for active treatment of hypertension, and closely monitor the blood pressure and other vital signs |
| Grade 5 | Death |  |

Note: Patients with hypertensive crisis should discontinue Apatinib permanently and withdraw from this clinical study.

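### Section 3.7.5 makes an apatinib stop mandatory only for massive gastrointestinal bleeding; a Grade 3-4 bleed elsewhere, including the nasopharynx or a neck vessel, is left to permissive and judgment-based rules

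*Protocol*

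**What the plan says.** Section 3.7.5 of the protocol has two triggers for acting on apatinib. One is a laboratory finding: "in case of severe abnormal coagulation function (grade 3 to 4), drug suspension is suggested". The other is a clinical event at one site: "If massive gastrointestinal bleeding occurs, Apatinib must be discontinued immediately". The section names no other bleeding site, attaches no CTCAE grade to a bleed, and does not say whether the gastrointestinal stop is permanent.

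Two general provisions also apply. Section 3.6 states: "The drug can only be suspended or its dose can only be reduced when a subject has grade III or worse adverse events" (it adds intolerable Grade II toxicity as a second ground). It limits interruptions: "the time of each drug suspension and the cumulative time of suspension during each administration cycle shall not be over 14 days". Section 3.4.4 tells the investigator to withdraw a patient who cannot tolerate drug toxicity (item 5), who meets item 6, "The subject develops unexpected or unacceptable drug-related adverse reactions", or for whom the investigator sees any other need (item 9).

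For hypertension, the table in 3.7.1 recommends suspension at Grade 3 and then says "reduce the dose of Apatinib and continue to use it if the blood pressure is well controlled"; at Grade 4 it says "Discontinue Apatinib immediately and permanently". The table in 3.7.2 recommends suspension at Grade 3 proteinuria, a reduced dose on recovery, and a permanent end if Grade 3 recurs after two reductions.

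**The concern.** This is a head-and-neck cancer trial of a VEGFR inhibitor, and haemorrhage outside the gut is the bleed that the protocol itself treats as potentially fatal. Section 1.4 reports two haemorrhage deaths in nasopharyngeal carcinoma patients on sunitinib and says that "the possible cause might be the rupture of large cervical vessels during tumor regression", which is an on-treatment mechanism. Section 3.4.2 item 5 excludes patients at high risk of fatal haemorrhage from important vessels. Item 6 uses a Grade 3 threshold at entry, without regard to site, for recent bleeds in patients with a severe haemorrhage history. Once treatment starts, no such threshold governs apatinib, and the only compulsory bleeding stop concerns the gut.

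At stake is consistent handling of a serious event. After the same Grade 3 nasopharyngeal bleed, one investigator may withdraw the patient under 3.4.4, a second may suspend apatinib, and a third may reduce the dose without a break. All three have followed the text.

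**Working it through.** The point depends on wording, so the check is to take a Grade 3-4 bleed outside the gut through every provision that could act on apatinib.

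1. **Section 3.7.5, gastrointestinal trigger.** Not met, because the site is wrong.
2. **Section 3.7.5, coagulation trigger.** Met only if the coagulation tests are also abnormal at Grade 3-4. A bleed from an eroded vessel need not come with such a result. Even when met, the action is only suggested.
3. **Section 3.6.** Applies, since the event is Grade III or worse. The sentence limits when a change is allowed; it does not order one. Suspension and reduction are alternatives, so reduction without interruption complies.
4. **Section 3.6, 14-day limit.** Leads to withdrawal only if a suspension was chosen and then ran too long. It does not start one.
5. **Section 3.4.4 items 5 and 6.** Directive once met, but the investigator must first find the toxicity intolerable or the reaction unexpected or unacceptable. Item 6 also requires the event to be drug-related. In the causality table of 3.9.4.3, an alternative explanation is marked as present only for the two unrelated categories. Tumour or earlier radiotherapy is an obvious alternative explanation for a neck bleed, so such a bleed could be classed as unrelated and item 6 would not apply.
6. **Section 3.4.4 item 9.** Always available, and wholly a matter of judgment.

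No step makes a bleeding-specific action mandatory.

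Apatinib action written for comparable grades:

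- Hypertension (3.7.1): Grade 3, suspend, then a reduced dose once controlled; Grade 4, immediate permanent stop.
- Proteinuria (3.7.2): Grade 3, suspend in the table. The running text of the same section is softer: for +++ protein or more than 3.5 g in 24 hours it says only to consider stopping.
- Transaminase and bilirubin elevation (3.7.9): Grade 3/4, suspension recommended.
- Bleeding outside the gut: Grades 3 and 4, nothing specific; the general rules in 3.6 and 3.4.4 only.

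The reduced doses that 3.6 permits are:

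- first step (500 + 250)/2 = 375 mg/day, and 375/500 = 75% of the starting dose;
- second step 250 mg/day, and 250/500 = 50%.

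These show what continued treatment would mean. They do not measure risk.

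**The case against.** The strongest reply is that the event is already covered. A reader might infer from 3.7.5 alone that a Grade 3-4 bleed outside the gut has no apatinib action at all. The protocol does not support that: 3.6 offers suspension or reduction for any Grade III event, and 3.4.4 directs withdrawal when its conditions are met. What is missing is a mandatory action specific to bleeding.

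The comparators also need care. The hypertension and proteinuria tables are headed as recommendations, and the proteinuria text only asks the investigator to consider stopping. Other parts of 3.7 (rash, marrow suppression, nausea) state no apatinib action, so leaving dose decisions to 3.6 is a common pattern in this protocol. That stands, and it weakens the claim that bleeding is singled out. It does not explain why 3.7.5, having chosen to write a compulsory bleeding stop, confines it to one site.

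A reader might also infer from Section 1.4 that a stop rule would have prevented the two deaths. It does not show this. Both patients had carotid sheath invasion and would be excluded here by 3.4.2 item 5, and no earlier non-fatal bleed is reported.

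Finally, few investigators would restart apatinib after a life-threatening neck-vessel bleed, and any such event would be reported as an SAE within 24 hours (3.9.5.4). That is fair for Grade 4. It has less force for a Grade 3 nasopharyngeal bleed, where reducing the dose and continuing is a more plausible decision.

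**Conclusion.** The point holds in a limited form. The only mandatory bleeding stop is restricted to massive gastrointestinal bleeding; at every other site a Grade 3-4 bleed meets a permissive rule and judgment-based withdrawal criteria. The text permits continued apatinib at a reduced dose after such a bleed, without directing it.

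The size is qualitative: no mandatory bleeding-specific action at Grade 3 or Grade 4 outside the gut, against a recommended suspension at Grade 3 and a permanent stop at Grade 4 for hypertension. The protocol gives no bleeding rate for eligible patients, so neither a number of patients affected nor a harm rate can be stated. The conclusion assumes that Section 3.6 is read literally, as permission rather than instruction. It has no bearing on alpha, power or sample size. This is a cheap patient-safety improvement, not an error that undermines the trial.

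**What to change.** In Section 3.7.5, replace the sentence that is limited to gastrointestinal bleeding with:

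> If massive gastrointestinal bleeding, or Grade 3 or worse bleeding at any site (including nasopharyngeal, oral or neck-vessel bleeding) occurs, Apatinib must be stopped immediately. For Grade 4 bleeding or any bleeding from a large neck vessel it must be discontinued permanently. After other Grade 3 bleeding it may be resumed at a reduced dose under 3.6 only once the bleeding has resolved, within the 14-day suspension limit.

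This keeps the existing gastrointestinal trigger. The Grade 4 stop follows the Grade 4 hypertension rule, and the recovery condition before resumption follows the Grade 3 hypertension and proteinuria tables. It needs no new tests, visits or patients. The downside is that a few patients may stop apatinib who would have tolerated continuing.

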### 3.7.6. Mouth Ulcers

Mouth ulcers caused by targeted drugs are usually discrete, ovoid, shallow, with clear boundaries and red surroundings. But some patients develop oral pain, dysgeusiae and swallowing difficulty rather than visible ulcers. Its pathogenesis has not yet been defined. Studies have shown that it is related to cell-mediated immunotoxicity and immune complex formation. It is also related to the declined VEGF level in the saliva. According to the literature, the incidence of mouth ulcers in patients using Sunitinib and Regorafenib was 25–38%, generally mild to moderate.

Apatinib and Capecitabine often cause mild to moderate mouth ulcers that can be controlled by symptomatic treatment. Few patients have severe or long-lasting mouth ulcers, in this case, the dose should be reduced or the treatment should be discontinued. It is recommended to educate patients to maintain oral hygiene and avoid eating hard, cold, hot or spicy food. Additionally, oral vitamin B can relieve mouth ulcers to a certain extent.

In the event of mild mouth ulcers, Yunnan Baiyao, Kangfuxin oral liquid, Yinlian gargle, Chlorhexidine oral ulcer mucous patch, or Beifuji spray, GeneTime spray, as well as Bing Peng San, Qing Dai San and Yangyin Shengji San are the preferred drugs. Patients with obvious oral pain can be topically added 2% Lidocaine and Sucralfate. For severe cases, corticosteroids or antibiotics can be used topically.

### 3.7.7. Bone Marrow Suppression

Antibiotics should be used for infection prevention when the neutrophil count was less than 0.5 × 10^9^/L, and patients with fever and coinfection should be treated with broad-spectrum antibiotics, such as granulocyte colony stimulating factors (G-CSFs).

In the event of transient thrombocytopenia (platelet count less than 50 × 10^9^/L), a small dose of glucocorticoid or Etamsylate can be used to prevent bleeding. When the platelet count is less than 20 × 10^9^/L, platelet transfusion, Etamsylate and hormones (e.g., Prednisolone) should be considered, as well as thrombopoietin (TPO) or interleukin to simulate the growth and differentiation of megakaryocytes when necessary.

### 3.7.8. Nausea, Vomiting and Loss of Appetite

Nausea and vomiting are common adverse events in patients with advanced tumors. Patients with mild to moderate symptoms can be given Metoclopramide/Metaline, while patients with severe symptoms need to be treated with 5-HT3 receptor blockers (Ondansetron, Granisetron, etc.), and patients with severe dehydration should be appropriately supplemented with fluids and electrolytes.

### 3.7.9. Hepatic Function Impairment

During treatment, patients should be regularly monitored for the hepatic function status. It is recommended to check liver function once every two weeks during the first two months of medication. Patients with severe hepatic function insufficiency are not allowed to use Apatinib and Capecitabine. For patients with elevated grade 3/4 transaminase and total bilirubin, it is recommended to suspend the drug, strengthen the symptomatic treatment to protect the liver and reduce the enzyme. Monitor the patient’s transaminase and total bilirubin levels and restore medication after such levels significantly drop, and also reduce the dose if the patient develops grade 3/4 adverse events again after restoration of medication.

## 3.8. Study Procedures

All patients will go through three stages of the screening period, treatment period and end of treatment period to complete this clinical study after signing the Informed Consent form. Before the study begins, all patients must read and sign the Informed Consent form approved by the Ethics Committee (EC). All study steps need to be performed within the time window specified in the trial flow chart. All observation indicators and time of examinations should not be affected by the length of drug discontinuity, and relevant examinations should be carried out in each corresponding course of treatment according to regulations.

### 3.8.1. Screening Stage

**1) Unless otherwise specified, the following screening procedures must be completed within 4 weeks before the study drug treatment starts:**

• Sign the Informed Consent form;

• Collect demographic data: Gender, date of birth, nationality, height, weight, etc.;

• Tumor diagnosis: Date of diagnosis, histological typing, lesion (primary or metastatic lesion), pathological stage TNM, clinical stage;

• Tumor treatment history:

a. Tumor surgery: Date and name of surgery

b. Radiotherapy history: Time and dose of radiotherapy received

c. Chemotherapy history and targeted treatment history: Name of the drug used, dose, medication cycle, start and end time, reason for dressing change (for dressing change due to disease progression, the imaging evidence should be recorded; for changing of therapies due to intolerance, adverse events and severity should be recorded), efficacy and outcome;

• Date of disease progress, relapse or metastasis after the last treatment;

• Complications treatment history: Including the treatment history of diabetes, hypertension, COPD, etc.;

• Blood pressure monitoring: During the screening period, the investigator will monitor the blood pressure of subjects. Before each blood pressure measurement, subjects are required to avoid smoking and coffee for 30 minutes and rest quietly for at least 10 minutes. During the measurement, they are required to be seated and maintain the elbow and the heart at the same level. Each blood pressure measurement is taken ipsilaterally.

• Imaging examination: Head, chest and abdominal CT or MRI. Bone scan is required when bone metastasis is clinically suspected;

(Written Informed Consent form must be obtained before any medical operation specified in the study. But CT/MRI scanning results obtained before signing the Informed Consent form to participate in this trial can be used for tumor evaluation during the screening period as long as they meet the requirements, provided that the date of such CT/MRI scanning must be within 28 days before the treatment)

• UCG: LVEF will be observed carefully; (Results of ECG examinations performed within 28 days before the signature of the Informed Consent form are acceptable)

• Concomitant medication and treatment: Concomitant medication and treatment within 28 days before enrollment and during the study period will be recorded.

• Record adverse events: From the date of signing the Informed Consent form, adverse events will be recorded regardless of whether the patient uses drugs or not.

